## Methods/design

### Subjects

The study has a parallel group design with an experimental group receiving treatment after baseline assessment and a waiting group receiving treatment after a waiting period of 16 weeks, comparably to the length of treatment. The planned allocation ratio is one expecting superiority in symptom reduction in the experimental group. Patients are recruited by licensed child and adolescent psychotherapists who work at the university hospital of Tübingen. A Google AdWords advertising and recruitment campaign is carried out in cooperation with the Department of Communication at the University Hospital Tübingen.

To deal with probable dropouts, we planned to enroll 30 children with OCD in the experimental group and 30 children with OCD in the waiting group with the aim to finally analyze 20 patients in each group. Including clinical considerations, this was a realistic sample size, we were able to achieve in a 3-year period. Sample size was planned according to the following considerations. As primary outcome, we considered the CY-Bocs score. Our primary assessment endpoint was the comparison at t1 post-treatment between the treatment and the waiting group. In the pilot study of our treatment protocol using a pre/post-assessment with *N* = 9 children with OCD [38], effect size was *d* = 2.02. Therefore, we knew, that our treatment protocol most likely will lead to symptom reduction. Effect size of another study comparing webcam-delivered CBT in 16 children with OCD with a waiting group of 15 children with an ANCOVA on post-treatment CY-Bocs scores, covarying baseline CY-BOCS scores, showed a significant effect of treatment with *η*^2^ = 0.36 [37]. A further study in adults with OCD [39], comparing face-to face exposure treatment (*n* = 20) with a waiting group (*n* = 16), revealed an effect size of *d* = 1.001 for the CY-Bocs comparison at post-treatment. Therefore, we estimated that the effect in our study as a comparison of CY-Bocs scores of an effective treatment in comparison to the waiting group at t1 will be high. We expected that there will be a significant difference comparing 20 patients with treatment with 20 patients in the waiting group at t1.

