### Statistical analysis

We will use SPSS for data analysis. For all diagnostic parameters, we will assess treatment efficiency with ANOVAs with group as the between-subject factor (treatment group (experimental group), waiting group (control group)) and time (t0 = diagnostic assessment, t1 = end of treatment treatment group/end of waiting period, t2 follow-up I treatment group/ end of treatment waiting group, t3 follow-up II treatment group/follow-up I waiting group, t4 follow-up II waiting group) as the within-subject factors. The most important outcome analysis will be the comparison in CY-Bocs score between the treatment and waiting group at t1. A comparable repeated measures ANOVA will be conducted for the time between t0 and t1 concerning weekly app questions/aggregated physiological data over the week but the time factor is week 1 to week 14. This is to indicate weekly symptom course and differences to the data assessed during waiting in the waiting group. Deeper analyses will concentrate on symptom course and intra-individual variability for daily app questions. Answers of child, parents, and therapist are correlated to investigate their agreement. Additionally, we will evaluate if avoidance behavior during exposures is related to treatment success within exposures with correlations of severity of avoidance behavior and anxiety decrease during exposures. We will also evaluate the influence of avoidance behavior during exposures and during the day on symptom decrease over the treatment assessed via CYBOCs with correlations. Descriptively, we evaluate the answers of our post-experimental questionnaire to treatment compliance, feasibility, and satisfaction as well as the within session questions. We will also compare the number of dropouts between the experimental group and the waiting group with *t*-tests. Integrity is descriptively evaluated with the session questionnaires provided by the therapist. Data will be analyzed to see if missing values are correlated with any basic effects. Little’s Missing Completely at Random Test (MCAR) will be used to check whether they are randomly distributed. The recommendations of the National Research Council will be followed. If there are missing data, we will report analyses with all data available. There will be enough data for the comparison between t0 and t1. A second set of analyses will also include the follow-up assessments where some missing data might appear. We might additionally report analyses with imputations. Significance will be followed up with Bonferroni-corrected paired contrasts. Alpha level is 5% and all tests will be conducted two-tailed.

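### Correlation is the planned measure of informant agreement but cannot show it, and the exposure correlations need a method that respects repeated exposures within a child

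*Protocol article*

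**What the plan says.** Three supplementary analyses in the Statistical analysis section of the protocol article matter here.

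- **Informants.** "Answers of child, parents, and therapist are correlated to investigate their agreement". The type of correlation is not named.
- **Exposures.** Whether avoidance goes with success within exposures is to be examined "with correlations of severity of avoidance behavior and anxiety decrease during exposures". A separate analysis takes up the "influence of avoidance behavior during exposures and during the day on symptom decrease over the treatment assessed via CYBOCs with correlations".
- **Dropouts.** "We will also compare the number of dropouts between the experimental group and the waiting group with *t*-tests".

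The general rule is "Alpha level is 5% and all tests will be conducted two-tailed".

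Other sections give the data structure. Under Apps, children and parents are both asked each evening about the child's symptoms, impairment and avoidance, and the app records distress and avoidance around each exposure. Under Manual/therapy sessions, there are 14 weekly sessions, exposure begins in session 4, and two sessions at the end add relapse prevention. Exposures are therefore repeated within a child. The Primary outcome section names the CY-BOCS group comparison at t1, which none of these analyses touches.

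**The concern.** For the informants, the stated question is agreement and the stated tool measures association. If parents score every item one step higher than the child, the two sets of answers can correlate perfectly and never coincide. A high correlation reported as agreement would hide exactly the level difference that a clinician combining child, parent and therapist reports needs to know about.

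For the exposures, a correlation fits one pair of values per independent unit. Here each child contributes several pairs. A correlation over all exposures would count them as independent and mix two questions: whether children who avoid more improve less, and whether a given child improves less in exposures with more avoidance. It could also give too small a p-value. The article fixes correlation as the method without saying which unit it applies to.

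**Working it through.** The documents give no figure for these analyses, so there is nothing to reproduce. The checks below use assumed values, shown as ranges.

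**1. Correlation against agreement**

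Lin's concordance coefficient, for two informants with SD ratio k and mean difference b (in SDs of the first informant), is CCC = 2rk / (1 + k² + b²). With equal SDs (k = 1) it is CCC = 2r / (2 + b²).

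For r = 0.9:

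| Assumed shift b | Calculation | CCC |
|---|---|---|
| 0 | 1.8 / 2 | 0.90 |
| 0.5 SD | 1.8 / 2.25 | 0.80 |
| 1 SD | 1.8 / 3 | 0.60 |
| 1.5 SD | 1.8 / 4.25 | 0.42 |

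Even r = 1.0 with a 1 SD shift gives 2 / 3 = 0.67. The reported correlation is the same in every row of the table.

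**2. Pooled exposures**

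Inputs: sessions 4 to 12 give 9 exposure sessions if the last two sessions are left out and each session has one exposure (assumption); 5 serves as a lower case. The ICC of avoidance and of anxiety decrease within a child is assumed to be 0, 0.3 or 0.5 in both variables.

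With m exposures per child and no true association, the variance of a pooled correlation is inflated by about DE = 1 + (m − 1) × ICC². The real error of a nominal 5% two-sided test is then about 2 × [1 − Φ(1.96 / √DE)].

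| m | ICC | DE | Approximate error | Simulated, pooled | Simulated, child means |
|---|---|---|---|---|---|
| 5 | 0.3 | 1 + 4 × 0.09 = 1.36 | 0.093 | 0.086 to 0.088 | 0.045 to 0.050 |
| 5 | 0.5 | 1 + 4 × 0.25 = 2.00 | 0.166 | 0.157 to 0.162 | 0.046 to 0.049 |
| 9 | 0.3 | 1 + 8 × 0.09 = 1.72 | 0.135 | 0.130 | 0.053 to 0.054 |
| 9 | 0.5 | 1 + 8 × 0.25 = 3.00 | 0.258 | 0.249 to 0.262 | 0.047 to 0.054 |

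The simulated columns cover 20 and 40 children, with 5,000 runs per setting. At ICC 0 the pooled test stays near 5% (0.047 to 0.055). One mean per child keeps the error near 5% throughout.

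The correlation with CY-BOCS decrease has one outcome per child, so this calculation does not clearly apply to it.

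**3. Dropout t-test**

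The Subjects section plans 30 per arm; the randomisation list of 8 blocks of 6 gives 48, or 24 per arm. Exact enumeration for 24 and 30 per arm, with the same dropout rate in both arms (5% to one third), gives the t-test on 0/1 data a type I error of 0.018 to 0.054. Its decision matched the uncorrected chi-square test in every scenario, including those with unequal rates. Fisher's test is more conservative (0.002 to 0.026). Example: 10/30 against 3/30 gives p = 0.028 (t), 0.028 (chi-square) and 0.057 (Fisher).

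**The case against.** **Informants.** The documents do not show that child, parent and therapist answer identical items on one scale. Where they do not, an absolute-agreement measure has no meaning and correlation is reasonable. This stands, and it limits the remedy to matched items. The size of any shift is also unknown; with no shift and equal SDs, concordance equals the correlation. That does not rescue the plan, because a correlation cannot reveal whether a shift exists.

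**Exposures.** A reader might infer that the plan ignores clustering and will therefore report false-positive avoidance effects. The text does not support this. It never says that exposures are pooled, and a condensed article may leave the unit of analysis to a fuller document. The same section uses repeated-measures ANOVA for the weekly app data and plans to study variability within individuals, so the authors know the structure. What remains is that success is to be judged within exposures, in a sentence separate from the one on change over the whole treatment. That points to exposure-level data, for which a simple correlation is unsuitable. If one value per child is meant, the test is valid but answers only the between-child question.

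**Dropouts.** A reader might infer that a t-test on a yes/no outcome gives wrong conclusions. At these sample sizes it does not: it decides as the uncorrected chi-square does. The gap to Fisher's test in the example reflects Fisher's conservatism.

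**Conclusion.** The agreement point holds: the named tool does not answer the named question. How much it misleads depends on the shift between informants, which is assumed here; at r = 0.9 with equal SDs, concordance runs from 0.90 with no shift to 0.42 at 1.5 SD.

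The exposure point holds conditionally. If exposures are pooled as independent, the type I error is about 9 to 13% at ICC 0.3 and 16 to 26% at ICC 0.5, under assumed ICCs and 5 to 9 exposures per child. With one summary per child it stays near 5%.

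The dropout t-test is a matter of form and presentation, not a source of error.

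The point is minor overall. It concerns supplementary questions and leaves the t1 CY-BOCS comparison untouched.

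**What to change.** - **Informants.** Where items match in content and scale (for example the child and parent app questions, if they do), report an absolute-agreement ICC or a concordance coefficient, plus the mean difference with limits of agreement. Elsewhere keep the correlation and call it association.
- **Exposures.** State the unit of analysis. For exposure-level data, fit a mixed model of anxiety decrease on avoidance with a random child effect, entering the child's mean avoidance and the deviation from that mean as separate terms. If only the between-child question is meant, say so and use one summary per child.
- **Dropouts (optional).** Give the risk difference between groups with a confidence interval, which tells the reader more than a t-test p-value.

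The cost is a few sentences of analysis wording. Every method runs on data already planned for collection, and sample size and the primary analysis do not change.

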## Background

The mental health of children and adolescents is a high-priority area and there is a need for effective and easily accessible treatments. Obsessive-compulsive disorder (OCD) is characterized by fear, worry-provoking intrusive thoughts, and repetitive behaviors that reduce the associated distress. Without treatment, OCD is a chronic and highly impairing disorder, with a population prevalence rate between 1 and 3% [1].

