Cognitive behavioral therapy (CBT) is a highly effective treatment for OCD in children and adults [2, 3]. During exposures with response prevention (ERP), patients are confronted with their intrusive thoughts and preceding situations; patients learn to stop their repetitive behaviors followed by a natural decline in distress and learning experience that intrusive thoughts are harmless. Unfortunately, there is limited availability of therapists adequately trained in this specific CBT procedure for OCD. In addition, ERP is hardly used during CBT because of practicability in everyday therapeutic life, or negative assumptions of the therapists, just to mention a few [4]. Apart from this, one major obstacle is also the fact that access to appropriate treatment is particularly difficult for children and adolescents in rural areas due to fewer psychotherapists being locally available [5. Accordingly, too few children with OCD get appropriate help [6]. Medication is much more accessible than CBT [7]. Another problem within face-to-face settings is that the psychotherapist often acts as security signal preventing a strong realistic symptom provocation. In addition, symptoms are especially present at home and, therefore, therapy should be more efficient, when these symptoms are treated in the corresponding triggering environment. OCD patients themselves also sometimes refuse psychotherapy due to avoiding behavior, fear of stigmatization, geographical distance to experts and time restrictions, especially in rural areas [8]. Patients, therefore, often suffer from a long delay until getting effective treatment. Late treatment onset is critical as the longer a patient is without effective treatment, the more likely their symptoms are to become chronic [9]. Accordingly, internet-based treatments with CBT experts could address an important gap in availability of treatments [10]. Moreover, due to the Covid-19 pandemic, psychotherapy was only possible via teleconferences which pushed acceptance of psychotherapists and patients forward for this new method more than ever before. iCBT could be especially attractive for pediatric patients as 90–96% of young people aged 12–24 have good internet accessibility and their ability to use new media platforms should be high [11]. It can be also cost-effective [12]. Furthermore, it may even be possible to reach and treat more patients across the country. The inclusion of parents in the therapeutic process is also more practical and easier via internet, as compared to traditional face-to-face approaches, as they can be part of the process no matter their location, as long as they have an internet connection.

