### Apps

We will use two apps for the project. The first app is an app with specific questions about the severity of children’s OCD and evaluations of the day or week. We will assess children and their parents with questions to the children’s OCD symptoms and impairment, avoiding behavior, mood, quality of the day, and daily hassles every day (in the evening). Furthermore, once a week, we will obtain in children’s and parents’ information about symptom development. Finally, the app prepares and evaluates exposures as well as levels of distress before, during, and after the exposures as well as avoiding behavior. Data of this app will be used for the therapy sessions and is discussed with the families. The second app will be a physiology app that connects the smartphone with a physiology wristband (BEURER AS 97). This app sends markers (e.g., beginning and end of exposures, beginning and end of bed time) and transfers the physiological data to save local storages at the university hospital. Data quality and entrance of the data into the hospital’s safe databases is continuously supervised and patients are reminded to complete the questions if they forgot it.

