Although our experience is very positive, there are several points that must be considered when conducting internet-based psychotherapy in patients. An important issue in such study approaches is surely the implementation and development of the data security concept and data transfer which required meticulous thought and work in the current study. Furthermore, the project was developed within intensive discussions in our international OCD experts work group to be able to deliver psychotherapy with such a high quality. Using technology of course also requires an effort by patients and therapists as well as continuous support with respect to technical problems (e.g., no internet connection of the smartphones, data delivery problems, video sessions cannot be started). It also must be noted that mobile internet in Germany has to be improved. Therefore, our app was developed in such a way that data transfer was minimal. Additionally, families are required to be equipped with WIFI access that is, however, mostly realized. It is also important to consider that webcams sometimes have the problem that the therapist cannot see everything in the room, especially with more family members involved. It is also not always possible to see if the patient focuses on the feared object during exposures. Therefore, it can sometimes be helpful to use 180 or 360° webcams or also eye tracker glasses to follow the gaze of the patients. Of course, we intend with our project to detect and to eliminate technological problems and to perfect the treatment manual which will then be easy to use by psychotherapists, including those with less experience of OCD therapeutic interventions. One further important point to be considered is the occurrence of unforeseen circumstances such as a case of emergency during teleconferences, which are beyond the control of the therapist. Then, it is important to contact the ambulance or police.

Finally, while the use of internet approaches is permitted, it is not yet confirmed whether all health insurance providers will pay for this type of therapy, which will impact the acceptability and distribution of these approaches. The Corona pandemic has paved the way for such contracts to begin to establish, perhaps hybrid approaches with both face-to-face and internet-based therapy elements could be the future.

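### The sign of the correlation between avoidance and within-exposure anxiety decrease does not show whether avoidance helps or harms, and the companion CY-BOCS correlation lacks baseline adjustment

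*Protocol article*

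**What the plan says.** In the protocol article, section Statistical analysis, the authors write that "we will evaluate if avoidance behavior during exposures is related to treatment success within exposures", and that they will do so "with correlations of severity of avoidance behavior and anxiety decrease during exposures". The outcome is thus the fall in anxiety within an exposure, and the predictor is avoidance in that exposure.

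The next sentence adds a second analysis: the "influence of avoidance behavior during exposures and during the day on symptom decrease over the treatment assessed via CYBOCs with correlations". Neither sentence states an adjustment for where the child started, whether in distress or in CY-BOCS.

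Other sections bear on how these correlations can be read:

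- Apps: one app records "levels of distress before, during, and after the exposures as well as avoiding behavior".
- Background, on the disorder: it involves "repetitive behaviors that reduce the associated distress".
- Background, on exposure with response prevention: "patients learn to stop their repetitive behaviors followed by a natural decline in distress".
- Background, on weak provocation as a drawback of office therapy: "the psychotherapist often acts as security signal preventing a strong realistic symptom provocation".
- Discussion, on webcam sessions: "It is also not always possible to see if the patient focuses on the feared object during exposures".

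**The concern.** On the article's own account, distress can fall for two opposite reasons. It can fall because the child carries out a behaviour that relieves it, or because the child refrains and the distress subsides naturally. Only the second is the therapeutic process. The planned marker counts both as success.

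If avoidance brings relief part-way through an exposure, it helps to produce the outcome it is correlated with, and r is pushed upwards. If avoidance keeps distress from rising at all, there is less to fall, and r is pushed downwards. The sign then reflects the timing and manner of avoidance as well as any effect on treatment.

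The CY-BOCS analysis has a different weakness. Children with a higher score at the start of treatment have more room to fall. If they also avoid more, raw decrease and avoidance correlate positively even when avoidance has no effect.

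At stake is what a paper may say about avoidance in exposure therapy, a central mechanism of the treatment. The efficacy conclusion is not at stake.

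**Working it through.** The article gives no sample size, power or expected r for these correlations, so there is no figure to reproduce. Every coefficient below is assumed and serves only to show what the planned statistic can do. A is avoidance with SD 1.

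**1. Relief and blunting, with harm only at the next exposure.** Peak distress = Z - p·A. Decrease = 0.4·peak + e·A + noise (SD 0.8). Distress at the next exposure = 0.3·A + noise (SD 1). Here e is immediate relief and p is blunted provocation.

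- True harm: r(A, next distress) = 0.3/√(0.09 + 1) = +0.29 throughout.
- Planned correlation: with k = e - 0.4p, r = k/√(0.16 + 0.64 + k²).
- e = 0.3, p = 0: k = 0.3, r = +0.32.
- e = 0.3, p = 0.5: k = 0.1, r = +0.11.
- e = 0.8, p = 0: k = 0.8, r = +0.67.
- e = 0.8, p = 0.5: k = 0.6, r = +0.56.
- e = 0, p = 0.3 to 0.5: k = -0.12 to -0.20, r = -0.13 to -0.22.

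**2. A model in which avoidance also impairs the decline within the exposure.** Learning L has correlation -h with A. Starting distress falls by p per SD of A. Decrease = 0.5·start + 0.5·L + e·A + noise (SD 0.7). CY-BOCS decrease = 0.7·L + noise (SD 0.7). Then k = e - 0.5h - 0.5p and r = k/√(0.25 + 0.25(1 - h²) + 0.49 + k²).

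| Relief e | Blunting p | r, h = 0.3 | r, h = 0.5 |
|---|---|---|---|
| 0 | 0 | -0.15 | -0.25 |
| 0.3 | 0 | +0.15 | +0.05 |
| 0.6 | 0 | +0.42 | +0.34 |
| 1.0 | 0 | +0.65 | +0.61 |
| 0 | 0.6 | -0.42 | -0.50 |
| 0.6 | 0.6 | +0.15 | +0.05 |

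In every row the correlation of A with CY-BOCS decrease is -0.21 (h = 0.3) or -0.35 (h = 0.5). Without relief the sign is correct. Without blunting it turns once e exceeds 0.5h, that is 0.15 or 0.25 per SD. Blunting alone keeps the sign but enlarges r.

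Adjusting for starting distress removes the blunting term but not the relief: the coefficient of A becomes e - 0.5h, for example 0.3 - 0.15 = +0.15. So adjustment improves the measure without making its sign interpretable as benefit or harm.

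**3. Raw CY-BOCS decrease with no effect of avoidance.** Let b be the correlation of avoidance with the starting score and r the pre-post correlation, with equal SDs. With no effect beyond the starting score, the correlation of avoidance with the end score is b·r. Then:

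- r(A, decrease) = (b - b·r)/√(2 - 2r) = b·√((1 - r)/2).
- b = 0.3, r = 0.5: 0.3 × 0.500 = +0.15.
- b = 0.3, r = 0.3: 0.3 × 0.592 = +0.18.
- b = 0.5, r = 0.5: 0.5 × 0.500 = +0.25.
- b = 0.5, r = 0.3: 0.5 × 0.592 = +0.30.

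With the starting score as covariate, the numerator of the avoidance effect is b·r - r·b = 0, so the spurious association disappears.

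**The case against.** The strongest reply is that decline within an exposure is the natural process measure of the article's own model, in which distress subsides once the behaviours stop. That stands, and it is a reason to keep the measure.

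Next, the Background ascribes distress reduction to repetitive behaviours and does not mention avoidance there. Extending it to avoidance is an inference, and no section says when avoidance occurs or how much relief it gives. The reversals in the working follow from assumed relief, and with none the sign is right. This also stands. A reader might infer that the planned analysis will show harmful avoidance as beneficial. The article does not support that; it supports only that the sign is not informative by itself.

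Third, the article tests avoidance against CY-BOCS decrease as well, and that clinician-administered outcome is not open to momentary relief. This limits the damage. But that analysis is unadjusted as stated, and its likely error, if sicker children avoid more, also points towards apparent benefit. The assumed correlation of 0.3 to 0.5 between baseline and avoidance has no support in the article. The entry criterion of a CY-BOCS above 16 narrows the baseline range and would tend to weaken it. The bias is proportional to b.

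Finally, one might want to replace the marker with distress at the next exposure. The article does not say that successive exposures are equally difficult. Under Manual/therapy sessions the therapist reviews the app data before each session, so the next exposure may respond to earlier avoidance. Restricting to avoidance-free exposures would remove the variation the question needs, and the Discussion concedes that attention to the feared object cannot always be seen.

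**Conclusion.** The point holds as a limit on interpretation and as a case for baseline adjustment. The article fixes same-exposure anxiety decrease as the success marker for avoidance, and by its own model a fall in distress need not be therapeutic. Under assumed coefficients with avoidance always harmful, the planned correlation runs from -0.50 to +0.67. Its size and direction in this trial are unknown. The CY-BOCS correlation can be spuriously positive by about +0.15 to +0.30, given assumed correlations of 0.3 to 0.5 for both baseline-avoidance and pre-post.

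These are additional analyses. A reader might infer that the trial's efficacy result is compromised. It is not, because the comparison of CY-BOCS between the groups at t1 does not use avoidance at all.

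**What to change.** 1. Replace the correlation with raw CY-BOCS decrease by a regression of end-of-treatment CY-BOCS on avoidance, with the CY-BOCS at the start of that group's treatment as covariate: t0 for the treatment group (end of treatment t1), t1 for the waiting group (end of treatment t2). Base any statement about benefit or harm of avoidance on this model, and describe it as an observational association.
2. Keep within-exposure anxiety decrease as a process measure only. Adjust it for the starting or peak distress that the app already records, and state in advance that no conclusion about benefit or harm is drawn from its sign.
3. Optionally, report distress at the next exposure as a sensitivity analysis, noting that exposures may differ in difficulty. It should not replace the marker.

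Items 1 and 2 change analysis wording only and use data already planned. Item 3 loses each child's last exposure, which has no successor. The change should be documented before these analyses are run.
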